# Safety and Efficacy of *Bojungikki-Tang* in Advanced NSCLC Patients Receiving Treatment with Immune Checkpoint Inhibitors: Protocol for a Multicenter, Double-Blind, Randomized, Placebo-Controlled Pilot Trial

**DOI:** 10.3390/ijerph20054507

**Published:** 2023-03-03

**Keywords:** *Bojungikki-tang*, immune checkpoint inhibitors, non-small cell lung cancer

## Abstract

Cancer immunotherapy with immune checkpoint inhibitors (ICIs) is a major treatment option for several types of cancer, including non-small cell lung cancer (NSCLC). The proposed study aims to investigate the safety and efficacy of *Bojungikki-tang* (BJIKT) therapy (an herbal medicine) in patients with advanced NSCLC treated with ICIs. This multicenter, randomized, placebo-controlled pilot study will be performed at three academic hospitals. Thirty patients with advanced NSCLC, undergoing atezolizumab monotherapy as second- and subsequent-line treatment, will be recruited and randomly assigned to either BJIKT treatment (atezolizumab + BJIKT) or placebo (atezolizumab + placebo). The primary and secondary outcomes are the incidence of adverse events (AEs), including immune- related AEs (irAEs) and non-immune-related AEs (non-irAEs); and early termination rate, withdrawal period, symptom improvement of fatigue, and skeletal muscle loss, respectively. The exploratory outcomes are patient objective response rate and immune profile. This is an ongoing trial. Recruitment started on 25 March 2022 and is expected to be completed by 30 June 2023. This study will provide basic evidence for the safety profiles, including irAEs, of herbal medicine in patients with advanced NSCLC treated with ICIs.

## 1. Introduction

Lung cancer causes the greatest number of deaths among all cancers worldwide, and the five-year survival rate for patients diagnosed with lung cancer is approximately 18% to 27% [1,2]. Non-small cell lung cancer (NSCLC), which accounts for 85% of lung cancers, is most frequently treated with immunotherapy [3]. Notably, immune checkpoint inhibitors (ICIs) have emerged as a major treatment for several types of cancer, including NSCLC.

ICIs, which are monoclonal antibodies targeting programmed cell death receptor 1 (PD-1) and programmed cell death ligand 1 (PD-L1), inhibit immune evasion mechanisms by blocking the PD-1/PD-L1 signaling pathway and reinvigorating T-cell activation. ICIs include anti-PD-1 antibodies, such as pembrolizumab and nivolumab; and anti-PD-L1 antibodies, such as atezolizumab. These medicines are used as standard treatments for advanced or metastatic NSCLC patients with no driver oncogenes (e.g., epidermal growth factor receptor (EGFR) and anaplastic lymphoma kinase (ALK)) [4].

However, despite their important clinical benefits, ICIs are associated with a unique spectrum of adverse reactions, termed immune-related adverse events (irAEs).

These irAEs include diarrhea/colitis, fatigue, nausea/vomiting, rash, and pruritus and may necessitate treatment discontinuation [5,6,7,8,9,10,11]. In a previous study of 61 NSCLC patients receiving ICIs, the discontinuation rate due to non-irAEs was 60%, and that due to irAEs reached 30% [5].

Moreover, when ICIs are used in combination with chemotherapy, the incidence of serious adverse events (AEs) of all grades and AEs above grade 3 were greater than for treatment with ICIs alone [6]. In addition, the combination of two ICIs or the combination of ICIs with cytotoxic chemotherapy is associated with higher rates of toxicity and increased severity of irAEs or treatment-related AEs [7,8]. Fatigue is one of the most common AEs of ICI treatment in lung cancer patients [6,9]. This symptom frequently occurs when atezolizumab monotherapy is administered to patients with advanced lung cancer (27%) [10].

*Bojungikki-tang* (BJIKT), also known as “*Bu-Zhong-Yi-Qi-Tang*” in China and “*Hochuekki-to*” in Japan, is one of the most commonly used herbal medicines for the treatment of various symptoms caused by gastric disorders (including fatigue, weariness, physical weakness resulting from illness, anorexia, and night sweats) in East Asian countries [12,13]. This herbal medicine is composed of *Ginseng Radix, Atractylodis Rhizoma Alba, Astragali Radix, Angelicae Gigantis Radix, Zizyphi Fructus, Bupleuri root, Citri Unshius Pericarpium, Cimicifugae Rhizoma, Zingiberis Rhizoma Recens, and Glycyrrhizae Radix et Rhizoma*. It has a bidirectional immunomodulatory effect that compensates for both excess and deficient conditions in treating cancer [14,15,16,17,18,19,20]. Many studies have reported on the safety of BJIKT, including its toxicity profile and long-term administration in cancer patients [21,22,23,24,25,26,27,28,29]. However, to our knowledge, no previous study has evaluated the irAEs of BJIKT in cancer patients treated with ICIs.

Therefore, in this protocol, we propose a randomized, placebo-controlled, double- blinded trial, to investigate the safety and efficacy for BJIKT in patients with advanced NSCLC who are concomitantly being treated with ICIs. Overall, this trial aims to: (1) investigate the safety of BJIKT in advanced NSCLC patients treated with ICIs in comparison with a placebo-controlled group; (2) evaluate post-treatment symptom improvement, focusing on fatigue and skeletal muscle loss in BJIKT and placebo-controlled groups; and (3) explore the feasibility of an integrative cancer treatment strategy by examining the patient immune status and objective response rate (ORR) following combined ICI and BJIKT treatment.

## 2. Materials and Methods

### 2.1. Study Design and Setting

This multicenter, randomized, placebo-controlled pilot study will be performed at Korea University Guro Hospital, Asan Medical Center, and Kyung Hee University Hospital (all located in Seoul, Republic of Korea). A total of 30 patients with NSCLC scheduled to undergo second- and subsequent-line monotherapy with atezolizumab, an ICI, will be recruited after obtaining their written informed consent. The enrolled participants will be randomly allocated into two parallel groups: BJIKT (atezolizumab + BJIKT) and placebo (atezolizumab + placebo). Patients will receive intravenous atezolizumab (at a 1200 mg fixed dose) every three weeks on day 1 of each three-week cycle [30]. According to the allocated group, patients will take BJIKT or placebo (4 g at a time) every day, regardless of withdrawal of the base drug, starting from the initiation of atezolizumab therapy. The trial will consist of three cycles administered over the course of approximately nine weeks, with a screening period and three study visits at three-week intervals. All participants will undergo the necessary examinations and testing procedures within four weeks prior to enrollment (i.e., prior to administering the investigational drug) according to the described clinical trial protocol.

The study period procedure is summarized in the Consolidated Standards of Reporting Trials (CONSORT) diagram (Figure 1), and this protocol is written in accordance with the recommendations of the Standard Protocol Items: Recommendations for Interventional Trials (SPIRIT) checklist. The schedule of enrolment, intervention, and assessments is summarized in Table 1.

### 2.2. Recruitment

Recruitment for this investigation began in March 2022 and is expected to end by June 2023. All participants will undergo a standardized interview and will receive clinical study information about the trial. Written consent will be obtained from all participants. The purpose, procedures, potential risks, and benefits of the study will also be thoroughly explained to the participants. The participants will be able to withdraw from the study at any time without any adverse consequences.

### 2.3. Participants

#### 2.3.1. Inclusion Criteria

Patients who meet all of the following criteria will be included in this trial: (1) adult male and female patients aged ≥19 years; (2) patients diagnosed with stage IIIB, IIIC, or IV NSCLC according to the TNM 8th edition diagnostic criteria; (3) patients scheduled to receive monotherapy with atezolizumab, an ICI, as second- and subsequent-line therapy (after providing their informed consent); (4) patients with advanced or metastatic NSCLC whose disease has progressed during or after approved platinum-based chemotherapy; (5) patients who are expected to survive for more than three months; (6) patients with an Eastern Cooperative Oncology Group (ECOG) performance status (PS) score of ≤2; (7) patients with measurable or evaluable lesions, as defined in the Response Evaluation Criteria in Solid Tumors (RECIST) version 1.1; (8) a hematological function evaluation showing a hemoglobin level of ≥9.0 g/dL, an absolute neutrophil count of ≥1500/µL, and a platelet count of ≥100 × 10^3^/µL; (9) renal function with a creatinine level of ≤1.5× the upper limit of normal (ULN), and creatinine clearance of ≥45 mL/min; (10) a liver function evaluation showing alanine aminotransferase (ALT) and aspartate aminotransferase (AST) levels ≤ 2.5× ULN; and (11) patients who voluntarily decide to participate and consent to study participation in writing after listening to and understanding a detailed explanation of the clinical trial.

#### 2.3.2. Exclusion Criteria

The study exclusion criteria are as follows: (1) diagnosis of a new primary cancer within the last five years; (2) treatment with an immunosuppressive drug within the last two weeks or ICI treatment within the last six weeks; (3) treatment with antibiotics within the last two weeks; (4) current treatment with thiazide or a loop diuretic; (5) the presence of hypokalemia; (6) a history of interstitial lung disease in the patient’s medical history; (7) confirmed EGFR or ALK gene mutations; (8) active autoimmune disease requiring systemic therapy within the last two years; (9) uncontrolled diabetes (i.e., diabetes that is uncontrolled with insulin or oral medication, based on fasting blood sugar levels); (10) uncontrolled hypertension; (11) heart defect; (12) active or untreated human immunodeficiency virus, tuberculosis, hepatitis B, or hepatitis C; (13) significant hematologic disease within six months before randomization; (14) abdominal cavity, esophageal atresia, or gastrointestinal-duct perforation within six months before randomization; (15) unresolved toxicity with a Common Terminology Criteria for Adverse Events (CTCAE) v5.0 level of >1 resulting from previous therapy at the start of the trial therapy; (16) serious hypersensitivity to ingredients in the investigational drug; (17) pregnancy or lactation; (18) among fertile women, lack of consent to use effective contraception for at least five months after the final administration of atezolizumab during the course of the clinical trial; (19) use of an oriental medicine or functional food that was determined by the investigator as having a potential to affect the trial or the patient’s safety within four weeks before initial treatment with the investigational drug; (20) participation in a clinical trial within four weeks before the first administration of the investigational drug; and (21) patients deemed unsuitable for this clinical trial by the investigator for various reasons, including serious infectious disease and organ failure.

### 2.4. Randomization and Allocation Concealment

A total of 30 eligible patients will be randomized into one of the two groups in a 1:1 ratio. An independent medical statistician will generate a random assignment code using the block randomization method with block sizes in SAS^®^ Version 9.4 (SAS Institute Inc., Cary, NC, USA). Each participant who satisfies the eligibility criteria will be assigned to the BJIKT treatment or placebo group at the baseline visit with a 1:1 allocation ratio.

The unique code derived for the random number table for each participant will be placed in an opaque sealed envelope and stored in double-locked cabinets. Labeling will be similar for both groups. We will maintain allocation concealment throughout the study period by providing participants with identically packaged, consecutively numbered drug containers.

### 2.5. Blinding

The proposed study will be a double-blinded trial wherein both participants and researchers, including nurses, physicians, and statisticians, will be blinded to the treatment allocation. Only an independent statistician will be aware of the group allocation and will have access to the randomization list and blinding codes.

### 2.6. Interventions

The BJIKT will be prepared by Hanpoong Pharm & Foods Co., Ltd. (Iksan, Republic of Korea). It will be produced according to the Korean Good Manufacturing Practice guidelines outlined by Korea Ministry of Food and Drug Safety (MFDS) and manufactured so that there is no difference between them in shape, color, smell, or taste. A blinded pharmacist will check the storage, dispensation, and quality of the investigational products. 

The BJIKT used in this study will be a dried, light yellowish-brown to fine brown granule extracted with water. The extract is composed of 10 medicinal plants, as follows: *Ginseng Radix* 1.33 g, Atractylodis Rhizoma Alba 1.33 g, Astragali Radix 1.33 g, *Angelicae Gigantis Radix* 1.0 g, *Zizyphi Fructus* 0.67 g, *Bupleuri* root 0.67 g, *Citri Unshius Pericarpium* 0.67 g, *Cimicifugae Rhizoma* 0.33 g, *Zingiberis Rhizoma Recens* 0.17 g, and *Glycyrrhizae Radix et Rhizoma* 0.5 g (representing the dose for one day of treatment).

The placebo will be made of water-immersed crude extract, lactose hydrate, corn starch, hydroxypropyl cellulose, sucrose fatty acid ester, magnesium stearate, and light anhydrous silicic acid. Both drugs will be identical in appearance, shape, taste, and color (brown). The BJIKT and placebo granules will be sealed in opaque aluminum bags and will be administered to the participants in 4g doses. 

All enrolled participants will receive intravenous atezolizumab (1200 mg fixed dose) every three weeks on day 1 of each three-week cycle and will take BJIKT or placebo (4 g at a time) every day for approximately nine weeks regardless of withdrawal of the base drug, starting from the initiation of atezolizumab therapy. This regimen may be discontinued according to the investigator’s judgment. All participants will be requested to return the remaining drugs in order to calculate compliance. All medications and treatments that are clinically determined to be necessary for the patient can be prescribed. The investigators will record the details of concomitant medication and treatment information in the case report form during this clinical trial period (from the date of clinical trial registration to the end of observation for each subject).

### 2.7. Outcome Measures

#### 2.7.1. Primary Outcomes

The primary study outcomes are the incidence of AEs, including irAEs and non- irAEs, and the incidence of AEs of CTCAE grade 4 or higher. These will be graded using the National Cancer Institute CTCAE v4.03 criteria [31].

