#### 2.7.4. Safety Outcomes

At each visit, all adverse reactions reported by the participant and observed by the investigator will be recorded, including those pertaining to vital signs and blood tests. All AEs (including irAEs) and ADRs related to ICI treatment in NSCLC patients will be descriptively recorded with detailed explanations, including information about the seriousness, severity, and causality of the events. Safety and tolerability will be assessed according to the National Cancer Institute Common Terminology Criteria (CTCAE v4.03). If possible, AEs collected during the trial period will be recorded using Medical Dictionary for Regulatory Activities (MedDRA) terms through a case report form.

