### 2.8. Sample Size

To our knowledge, this is the first exploratory clinical trial to investigate the improvement in symptoms and AEs following BJIKT treatment as compared to placebo in patients with advanced NSCLC who are being treated with ICIs.

Considering the exploratory nature of the clinical trial and the number of patients available from each center, a total of 30 participants (15 in each group) will be enrolled. Recruitment started on 25 March 2022 and is expected to be completed by 30 June 2023.

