### 2.9. Statistical Analysis

All statistical analyses will be performed using a two-tailed test with a 5% level of significance. An independent statistician will conduct statistical analysis using SAS^®^ Version 9.4 (SAS Institute Inc., Cary, NC, USA). 

The primary efficacy variable will be summarized using the full analysis set (FAS), and the per-protocol set (PPS) will be used for a supportive analysis. All other efficacy analyses will be based on the FAS. Safety variables will be summarized using a safety set (SS), which includes all participants receiving at least one dose of the study medication. The FAS will consist of all randomized participants who received at least one dose of the study medication and who underwent a valid measurement of the primary efficacy variable at baseline.

The PPS will consist of all participants in the FAS who showed no important protocol deviation affecting the primary efficacy variable.

Participants showing important protocol deviations will be predefined and evaluated during a data evaluation meeting prior to unblinding the data.

Categorical data will be presented as frequencies and percentages, and continuous data will be presented as means and 95% confidence intervals. 

The normality of continuous variables in the clinical data will be tested using the Kolmogorov–Smirnov test. Continuous data will be analyzed using the independent t-test or Wilcoxon rank-sum test, and categorical data will be analyzed using the chi-squared test or Fisher’s exact test for comparison of two groups. Mixed-effect model repeated measures (MMRM) will be used, with each group and visit time as fixed factors and subjects as random factors. Paired *t*-tests or Wilcoxon signed rank tests will be used to compare the factors before and after treatment. 

Pearson’s correlation or Spearman’s rank correlation tests will be used for each administration group in order to examine the correlations among various immune indicators measured in blood samples, treatment responses, and each identified pattern. The data collected in this study will be used as is for analysis without replacing or imputing missing values. 

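### If the placebo rate is high, the any-grade AE primary has little room to show an increase, and neither primary registers an all-cause shift from grade 1–2 to grade 3

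*Protocol article*

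**What the plan says.** Section 2.7.1 (Primary Outcomes) reads: "The primary study outcomes are the incidence of AEs", taking irAEs and non-irAEs together, and adds AEs of grade 4 or higher as a second primary. The first component has no grade floor and no restriction to related events. Section 2.7.4 (Safety Outcomes) collects participant-reported and investigator-observed reactions, including those in vital signs and blood tests, "including information about the seriousness, severity, and causality of the events".

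Section 2.8 sets the size: "a total of 30 participants (15 in each group) will be enrolled". It rests on the exploratory purpose and on how many patients the centers can supply; no AE rate, effect size or power is given. Section 2.9 says "All statistical analyses will be performed using a two-tailed test with a 5% level of significance" and "Categorical data will be presented as frequencies and percentages", with chi-squared or Fisher's exact test for comparing the groups.

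Grade 3 appears only among the secondary outcomes (section 2.7.2): early interruption due to AEs of grade 3 or above, and adverse drug reactions of grade 3 or above.

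**The concern.** Every patient has progressed on platinum-based chemotherapy (section 2.3.1) and every patient receives atezolizumab (section 2.6). The Introduction cites 27% for fatigue alone on atezolizumab monotherapy. It is therefore plausible that most placebo patients will have at least one AE of some grade within about nine weeks. A yes/no variable that is already high has little room to rise: at a true placebo rate of 90%, the largest possible increase is 10 percentage points.

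The first aim in the Introduction is to compare safety with placebo. If both arms report similar, high any-AE percentages, this could be read as reassurance even if BJIKT had moved patients from mild to grade 3 events. The second primary starts at grade 4, so it would not register that movement either.

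**Working it through.** **Inputs.** From the article: 15 per arm (2.4, 2.8); two-sided 5% level, chi-squared or Fisher (2.9). Assumed: the placebo any-AE rate, the grade distribution and the size of harm. There is no stated design figure to reproduce.

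**1. Where the any-AE comparison runs out of room.** Let all 15 BJIKT patients have an AE and let k placebo patients have none. Fisher's one-sided p is C(15,k)/C(30,k); with equal arms the two-sided p is twice that. Uncorrected chi-squared is 30k/(30−k).

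| Placebo with AE | k | Fisher two-sided | Chi-squared, p |
|---|---|---|---|
| 10/15 | 5 | 2 × 3003/142506 = 0.042 | 6.00, 0.014 |
| 11/15 | 4 | 2 × 1365/27405 = 0.0996 | 4.62, 0.032 |
| 12/15 | 3 | 2 × 455/4060 = 0.224 | 3.33, 0.068 |

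At 11/15 the expected number without an AE is 15 × 4/30 = 2 per arm, so Fisher is the conventional choice. The choice of test moves the limit by one patient.

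**2. How likely that is.** With the placebo count X binomial (15, p), P(X ≥ 11) is 22% at p = 60%, 69% at 75% and 99% at 90%. If every BJIKT patient has an AE, Fisher power for an increase is 1 − P(X ≥ 11): 78%, 31% and 1.3%.

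**3. The other primary.** Grade 4+ has no ceiling: 5/15 v 0/15 gives p = 0.042 and 4/15 v 0/15 gives 0.0996.

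**4. A general shift in severity.** Assume placebo worst grades 0 to 5 of 10/25/35/22/6/2% (90% any AE) and a common odds ratio of 5. Grade 3+ then goes from 30% to 68%: odds 0.30/0.70 = 0.429; × 5 = 2.143; 2.143/3.143 = 0.68. For the 60% case, grades 1 to 5 are scaled by 60/90. Fisher powers are exact; Wilcoxon powers are simulated with 20,000 trials.

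| Assumption | Any AE | Grade 4+ | Grade 3+ | Worst grade, Wilcoxon |
|---|---|---|---|---|
| 90% any AE, odds ratio 5 | 1% | 20% | 39% | 63–65% |
| 60% any AE, odds ratio 5 | 27% | 11% | 35% | 65% |

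The Wilcoxon test falls to about 36% at an odds ratio of 3, 16–17% at 2 and 9% at 1.5 (90% case).

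**5. Where worst grade does worse.** In an illustration where events move only between none and grade 1–2, any-AE has 54% power and Wilcoxon 27%. Where harm is concentrated at grade 4 and above (grade 4+ from 8% to 38%), the grade 4+ primary has 35% and Wilcoxon about 10–12%, depending on which grades the cases come from.

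**The case against.** A reader might infer that the primary outcome cannot show harm. The article does not support that. It gives no any-grade AE rate. The 60% and 30% in the Introduction are discontinuation figures from one study of 61 patients, with denominator and follow-up unstated, and they do not set a floor for AE incidence here. At a true rate of 60%, placebo reaches 11 of 15 in only 22% of trials, so the ceiling usually would not bind.

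A reader might also infer that severity is thrown away. It is not: grade 4+ is itself a primary, grade 3+ drug reactions and interruptions are secondaries, and severity is recorded for every event. What remains is narrower. The grade 3+ outcomes cover drug-related events or interruptions, not all-cause AEs, and they are not primary.

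Third, a reader might want worst grade to replace the primary. Step 5 shows why that would be a trade-off, and the odds ratio of 5 is a large effect under a model that suits the Wilcoxon test. Much of the low power comes from having 15 per arm.

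It is also fair that the tests are two-tailed and a high placebo rate leaves room to show a reduction (54% Fisher power for 90% to 50%), and that this is a declared pilot with no power claim, whose Discussion says larger trials are needed to confirm safety. That makes significance a poor yardstick. The limited room affects estimates as well, however: the risk difference cannot exceed one minus the placebo rate.

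**Conclusion.** The point holds in a limited form. The 11-of-15 limit is exact for Fisher (12 of 15 for uncorrected chi-squared). Whether it matters depends on a placebo rate that the article does not give: it matters little at 60%, often at 75% and almost always at 90%. It applies to one pooled percentage and to showing an increase. The firmer finding needs no assumed rate: with one primary at any grade and the other at grade 4 or higher, an all-cause movement from grade 1–2 to grade 3 changes neither. For a general severity shift of the size assumed, worst grade is the more sensitive measure at both 60% and 90% any-AE, but not when harm is confined to the lowest or highest grades. This is a weakness in what the primary outcomes can register, not a wrong figure in the plan.

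**What to change.** Keep both stated primaries and report each with an estimate of the difference and its 95% confidence interval. Add to sections 2.7.1 and 2.9, before unblinding, one pre-specified comparison of worst CTCAE grade per patient (0 = none, to 5) by Wilcoxon rank-sum for all AEs. Report the probability that a BJIKT patient has a worse grade than a placebo patient, with its 95% confidence interval. Show irAEs and non-irAEs as descriptive breakdowns, so that no further tests are added. State that similar any-AE percentages alone will not be taken as evidence of safety.

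The grades are already collected, so the cost is wording and one more analysis, with no new data and no change to the stated primaries. The downsides are a less familiar effect measure and the loss of sensitivity to harm confined to one end of the scale, which is why both existing primaries should stay.
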